### Data collection

#### Blood samples

Venous blood samples (of approximately 25 mL) will be collected under medical supervision using the BD Vacutainer® Butterfly Safety Lok, EDTA tubes and SST™ II Advance serum tubes (Becton Dickinson, Heidelberg, Germany). For the evaluation of the chosen parameters, participants are not required to be fasted. A haemogram will be measured from the EDTA blood using a Sysmex KX-21N automated haematology analyser (Sysmex Deutschland GmbH, Bornbach, Germany). Two serum samples will be centrifuged at 4000×*g* for 10 min and pipetted and stored at − 80 °C in the Center for Molecular Medicine Cologne (University of Cologne, Germany) until it will be analysed. The thawed serum samples will be used to measure the following cytokines by multiplex ELISA (Bio-Plex Pro Human Cytokine 8-plex ELISA Kit, Bio-Plex Pro Human Chemokine IL-1β Singleplex Set; Bio-Rad Laboratories GmbH, Munich, Germany): tumour necrosis factor-alpha, interleukin-6, interleukin-8 and interleukin-1β.

#### Saliva samples

Saliva samples will be collected after a 30-min fast via Salivettes® from Sarstedt (Sarstedt AG & Co. KG, Nümbrecht, Germany). Samples will be centrifuged at 4000×*g* for 10 min and pipetted and stored at − 80 °C in the Center for Molecular Medicine Cologne (University of Cologne, Germany). The following selected cytokines will be analysed by a multiplex ELISA (Bio-Plex Pro Human Cytokine 8-plex, Bio-Rad Laboratories GmbH, Munich, Germany): tumour necrosis factor-alpha, interleukin-6, interleukin-8 and interferon-gamma.

#### Faecal samples

Faecal analyses will be carried out at the Institute of Microoecology, Herborn, Germany. Faecal samples will be collected during the final day of the dietary programme. Subjects will be given a sterile stool sampling kit and detailed sample collection instructions. Subjects will send samples to the laboratory, and if shipping is not possible immediately after collection, the sample will be stored in a refrigerator at 7 °C but will be sent on the same day.

#### Nutritional data

Each participant will complete four detailed 7-day food diaries based on self-reported intake prior to the next faecal sample collection. A standardised protocol will be developed by a research dietitian supervisor. Subjects will maintain a habitual diet, such that potential gastrointestinal modifications can only be attributed to the intervention of sports or probiotics.

Nutritional quality and quantity of consumed foods and drinks as well as nutritional supplements will be recorded. A prepared protocol with instructions will help to guide the data recorded: breakfast, lunch, dinner, snacks, recipe information, preparation method (raw, steamed, boiled, fried, breaded, baked, with/without skin), fat/fructose content and food amount (gramme/millilitre).

Dietary data and personal data (gender, age, body height, body weight, body mass index) will be entered into the DGExpert software (version 1.8.9.0) to generate each subject’s energy and nutrient intake as well as respective reference values.

The following list of dietary parameters will be analysed each day in grammes/microgrammes/percentage:Energy/caloric intake (kilocalories, kilojoule)ProteinsFatsTotal fatty acidsPolyunsaturated fatty acidsMonounsaturated fatty acidsSaturated fatty acidsLinoleic acidLinolenic acidQuotient of linoleic acid to linolenic acidTotal carbohydratesAbsorbable carbohydratesFibresLactoseSucroseMonosaccharidesDisaccharidesTotal sugarAll vitamins and micronutrientsWaterAlcohol

### Laboratory procedures

#### Identification and enumeration of microorganisms

Bacteria will be enumerated using the KyberKompaktPro® test, which combines the identification of viable bacteria by classical microbial analysis and quantitative polymerase chain reaction (qPCR).

Viable bacteria will be enumerated on the following selective media: Columbia blood agar (total cell count; BioMérieux, Nürtingen, Germany), U3G agar (*Enterobacteriacae*, *enterococci*; Heipha, Heidelberg, Germany), Rogosa agar, (*Lactobacilli*; Heipha), DIC agar (*Bifidobacteria*; Heipha), Schaedler agar (*Bacteroides*; Heipha) and SPM agar (*Clostridia*; Heipha). Faecal samples will be serially diluted in 1 mL of phosphate-buffered saline (PBS, pH 7.2) and subsequently plated on selective agar plates by a fully automated spiral plater (PreviIsola, BioMérieux). The plates will be incubated under either aerobic or anoxic conditions at 37 °C for at least 2 days. Bacteria will be identified by gram staining and colony morphologies. Additionally, identifications will be performed by the API and VITEK systems (BioMérieux). All counts will be recorded by the number of log_10_ CFU per grammes of sample.

The following bacteria will be routinely analysed: *Clostridium* spp., *Bifidobacterium* spp., *Bacteroides* spp., (*E. coli*, *Enterococcus* spp., *Lactobacillus* spp.) and other bacteria (*Pseudomonas* spp., *Klebsiella* spp*.*, *Proteus* spp., *Citrobacter* spp*., Enterobacter* spp., other aerobic bacteria).

#### DNA extraction from faecal samples for further qPCR analysis

Microbial DNA will be extracted from 200 mg of faecal samples using the QIAsymphony® DSP Virus/Pathogen Mini-Kit (Qiagen, Hilden, Germany) following the manufacturer’s instructions on the QIAsymphony® SP (Qiagen). Automated isolation and pipetting of 96-well plates (MicroAmp Optical 96-Well Reaction Plate, Applied Biosystems, Darmstadt, Germany) will be performed by the QIAsymphony® SP/AS instrument (Qiagen) using the QIAsymphony DSP Virus/Pathogen Mini-Kit.

#### Quantification of target bacteria by quantitative real-time PCR (qPCR)

Primers will be selected to recognise the phyla *Firmicutes*, *Bacteroidetes* [43], *Verrucomicrobia*, the genus *Enterobacteriacea* [44] and *Methanobrevibacter* as well as the species *Faecalibacterium prausnitzii* and *Akkermansia muciniphila*.

PCR amplification and detection will be performed using an ABI PRISM 7900HT sequence detection system (Applied Biosystems, Darmstadt, Germany) in optical-grade 96-well plates sealed with optical sealing tape. Each reaction mixture (25 μL) will be composed of 12.5 μL of QuantiTect SYBR Green PCR Master Mix (Qiagen), 2 μL primer mix (10 pmol/μL each), 9 μL sterile distilled H_2_O and 1.5 μL stool DNA (10 ng/μL). For the negative control, 2 μL of sterile distilled H_2_O will be added to the reaction solution instead of the template DNA solution. A standard curve will be produced using the appropriate reference organism to quantify the qPCR values into the number of bacteria per grammes. The standard curves will be prepared in the same PCR assay as the samples. The fluorescent products will be detected in the last step of each cycle. A melting curve analysis will be carried out following amplification to distinguish the targeted PCR product from the non-targeted PCR product. The melting curves will be obtained by slowly increasing the temperature to 55 and 95 °C at a rate of 0.2 °C/s, with continuous fluorescence collection. The data will be analysed using ABI Prism software. The real-time PCRs will be performed in triplicate, and average values will be used for enumeration.

#### Laboratory analyses of short-chain fatty acids

Human stool samples analysed for short-chain fatty acid (SCFA) content will be freeze-dried and subsequently analysed using a gas chromatograph. The samples will be weighed (~ 200 mg of dry matter) and a 10-fold dilution with physiological NaCl saline (1.8 mL) will be produced. Following vortexing (2 min, Vortexer MS 3 basic, IKA-Werke GmbH & Co. KG, Staufen, Germany), an aliquot of 200 μL will be mixed with 0.36 M HClO_4_ (280 μL) and 1 M NaOH (270 μL). The solution will be lyophilised at − 35 °C (alpha 1–4 LSC, CHRIST, Osterode am Harz, Germany). The obtained lyophilisate will be dissolved in 100 μL 5 M HCOOH and 400 μL acetone and centrifuged (5 min at 4000×*g*, RT; Pico 17, Thermo Electron LED GmbH, Langenselbold, Germany). Concentrations of the SCFA will be determined in the supernatant using a GC-2010 Plus gas chromatograph (Shimadzu Deutschland GmbH, Duisburg, Germany) equipped with flame ionisation detection and a thin-film capillary column Stabilwax®-DA 30 m × 0.25 mm × 0.5 μm (Restek, Bad Homburg, Germany). The samples will be spread out by split injection using the auto-sampler AOC-20s/I (Shimadzu Deutschland GmbH). GCsolution Chromatography Data System (Shimadzu Deutschland GmbH) will be used for data processing. For the determination of the SCFA, an external standard (Supelco™ WSFA-1 Mix, Supelco Sigma-Aldrich Co., Bellefonte PA) will be used.

#### Laboratory analyses of faecal markers

Faecal calprotectin, eosinophil protein x (EPX), zonulin, beta-defensin 2 (β-defensin 2) and secretory immunoglobulin A (sIgA) concentrations will be measured by an ELISA kit (Immundiagnostik AG, Bensheim, Germany). The tests to analyse calprotectin and EPX use the sandwich ELISA technique. Monoclonal anti-calprotectin-antibodies or anti-EPX-antibodies will be added to the samples, standards and controls. Colour intensity is directly proportional to the concentration of calprotectin and EPX. Samples will be read at 450 nm. Standard curves will be formed by the four-parameter algorithm.

A competitive binding technique will be used to determine zonulin concentrations. Samples, standards and controls will be added with biotinylated zonulin and incubated with polyclonal anti-zonulin antibodies. Colour intensity is inversely proportional to the sample concentration of zonulin. Samples will be read at 450 nm. The four-parameter algorithm will be used to create the standard curve [45].

Quantitative analysis of β-defensin 2, standards and controls will be performed using polyclonal anti-β-defensin 2 antibodies. The amount of bound enzymes is directly proportional to the β-defensin 2 content. Samples will also be measured at 450 nm.

To determine secretory immunoglobulin A (sIgA), polyclonal anti-sIgA antibodies will be added to the samples. The test uses a calibrator and calibration curve to detect sIgA content. Colour development is proportional to the amount of analyte.

Faecal alpha-1-antitrypsin concentrations will be measured using the AAT test (Maier Analytic, Sinsheim, Germany). The assay uses the sandwich technique and polyclonal antibodies will be utilised to analyse samples, standards and controls. Colour intensity is directly proportional to the alpha-1-antytrypsin concentration in the sample. The samples will be read at 450 nm and the standard curve formed via the four-parameter algorithm.

### Sample size

It is estimated that a sample size of a minimum of 30 participants is required in order to provide a pooled standard deviation that provides enough precision for the development of a future trial [46, 47].

### Participants and recruitment

The study will have a half-year enrollment phase. Recruitment will be carried out by the study director. Healthy students with an age between 18 and 29 and a body mass index of ≤ 25 kg/m^2^ will be recruited through bachelor endurance courses at the German Sport University Cologne (maximal number of participants around 320 students). Therefore, our feasibility study enrollment rate has to exceed 10%. The recruitment rate will be analysed by the number of eligible individuals recruited within half a year, as presented above. A recruitment rate of > 80% will be considered as feasible to conduct a future randomised control trial.

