**Methods:**

In this pilot study, thirty non-specifically trained student athletes will participate in an intervention consisting of a two-week rest (baseline) period, a four-week exercise programme and a four-week probiotic intervention using SymbioLactComp®. The exercise programme consists of three 60-min running workouts per week at 70–85% of the peak heart rate (HRpeak). Primary endpoint of this pilot study is the feasibility and practicality of the intervention as well as a sample size estimation. Furthermore, anthropometric measurements and information on nutrition and lifestyle will be obtained. The peak oxygen uptake (VO_2_peak) and peak heart rate (HRpeak) (determined during a shuttle run test) as well as selected blood and saliva parameters (haemogram, cytokines) will be evaluated. Changes to the intestinal microbiota will be analysed by stool diagnostics (KyberKompaktPRO®, KyberPlus®). The potential changes may include microbiota composition, bacterial metabolites and mucosa- and immune markers.

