### Statistical analysis

This pilot study intends to examine the confidence interval estimation and feasibility of the presented approach (physical activity and probiotic supplementation) [49, 50]. Attendance and retention rates will be assessed to calculate adherence. Attendance rate will be analysed by dividing the mean value for the number of participants present by the number of sessions offered during the four-week exercise period and the four-week probiotic intervention. The retention rate will be analysed by the percentage of participants completing all sessions of the endurance training (twelve in total), shuttle run test (two in total), nutrition questionnaire (four in total), blood/saliva measurement (four in total) and stool diagnostics (four in total) present in each step of the study. A retention rate of > 80% will be considered as feasible to conduct a future randomised controlled trial. Hypothesis testing and results of regression modelling will be considered entirely exploratory in nature and interpreted with caution. Our trial is mainly conducted in preparation for a future definitive randomised controlled trial to assess the efficacy of the intervention/study design [51]. All data will be entered into the database management software and analysed by the SPSS Version 25.0 (SPSS Inc., Chicago, IL, USA). The Shapiro-Wilk test will be used for variable normal distribution and the usual descriptive statistics for background information and mean values with a 95% confidence interval. Data will be used for sample size estimation and to determine the most appropriate outcome measure for the main study. Descriptive statistics and confidence intervals will also be calculated to examine the trends in the analysed parameters. This information will help to identify which parameters to focus on in future trials. Depending on the normality of the underlying data, parametric or non-parametric (e.g. unpaired *t* test/Mann-Whitney *U* test) tests will be carried out. Furthermore, a paired *t* test/Wilcoxon test might be computed for the longitudinal comparison (T0–T3). Bivariate correlation analyses might be assessed by the Spearman/Pearson correlation coefficient. Multivariate analyses with linear or logistic regressions might be performed to explore potential effects of the intervention and further potential covariates and cofactors. Moreover, multiple regression models might be used if multiple variables are predictive. The level of statistical significance is *p* < 0.05.

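### The two recruitment thresholds do not fit the planned size as written: 30 of about 320 is 9.4%, just short of the 10% to be exceeded, and the > 80% progression rule has no stated denominator

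*Protocol article*

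**What the plan says.** All references are to the protocol article.

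- **Size.** The Sample size section states that "a sample size of a minimum of 30 participants is required". The Methods paragraph of the Abstract plans for the same number: "thirty non-specifically trained student athletes will participate in an intervention".
- **Pool.** Participants and recruitment gives the source population as bachelor endurance courses, "maximal number of participants around 320 students".
- **First threshold.** The next sentence draws a conclusion from that pool: "Therefore, our feasibility study enrollment rate has to exceed 10" per cent.
- **Second threshold.** The same paragraph then changes term, from enrolment rate to recruitment rate, and describes it by a count: "The recruitment rate will be analysed by the number of eligible individuals recruited within half a year, as presented above". It continues: "A recruitment rate of > 80% will be considered as feasible to conduct a future randomised control trial".
- **Retention.** The Statistical analysis section sets a separate criterion at the same level: "A retention rate of > 80% will be considered as feasible to conduct a future randomised controlled trial". That rate is described as a percentage of participants completing listed procedures.

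Feasibility is the primary outcome (Aims and objectives), and the Discussion relies on the progression criteria as a basis for the main trial.

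**The concern.** One short paragraph contains two similarly named rates with thresholds of 10% and 80%, and does not say how they differ. The first threshold is presented as following from the pool, yet the trial's own planned size falls just below it. The second decides whether a main trial is feasible, yet only its numerator is described.

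A progression criterion is useful only if the result could be read off by someone who had no part in choosing it. Here the denominator would have to be chosen when the count is already known, and that choice can decide whether the pilot is declared feasible. Recruitment and retention are the outcomes for which the article gives numerical thresholds, so this ambiguity affects a substantial part of the primary outcome.

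**Working it through.** **Inputs.** Planned and minimum size 30 (Sample size; Abstract). Pool around 320, given as a maximum (Participants and recruitment). Thresholds > 10% and > 80% (same section).

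**Step 1: where the 10% comes from.** 30/320 = 0.09375, or 9.4%. The plan's 10% appears to be this figure rounded up. In reverse, 0.10 × 320 = 32, within two participants of 30.

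**Step 2: does the planned size meet it?** The wording is a strict inequality.
- 30/320 = 9.4%: fails.
- 32/320 = 10.0%: equals the threshold and does not exceed it.
- 33/320 = 10.3%: the first count that passes.
- With exactly 30 recruits, the pool must be 299 or smaller: 30/299 = 10.03% passes, 30/300 = 10.0% does not.

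The shortfall is three participants, or 10 − 9.4 = 0.6 percentage points.

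**Step 3: what the 80% rule requires, by denominator.**

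| Denominator | Requirement for > 80% | Consequence |
|---|---|---|
| Pool of 320 | 0.80 × 320 = 256, so at least 257 recruits | 257/30 = 8.6 times the planned size |
| Eligible students, 30 recruited | 30/0.80 = 37.5, so at most 37 eligible (30/37 = 81.1%; 30/38 = 78.9%) | 37/320 = 11.6% of the pool |
| Eligible students, 33 recruited (the 10% rule also met) | at most 41 eligible (33/41 = 80.5%; 33/42 = 78.6%) | 41/320 = 12.8% of the pool |
| Target of 30 | 0.80 × 30 = 24, so at least 25 recruits (25/30 = 83.3%) | 25/320 = 7.8%, which fails the 10% rule |

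**Step 4: how sensitive is the eligible-student reading?** The article gives no eligible share, so the following is an assumed range for illustration. If 25% of 320 were eligible (80 students), > 80% means more than 64, so 65 recruits. If 50% were eligible (160 students), it means more than 128, so 129 recruits. A pilot of about 30 passes on this reading only if few of the 320 are eligible.

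**Step 5: one result, different verdicts.** Suppose exactly 30 are recruited from 320. The 80% rule fails on the pool (9.4%), passes on the target (100%), and on eligible students passes with 37 eligible and fails with 38. The text does not say which applies.

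**The case against.** The best defence is that the two rates are different quantities. The enrolment rate follows from the pool of 320, while the recruitment rate is described through eligible individuals: "The recruitment rate will be analysed by the number of eligible individuals recruited within half a year". The 320 are course members, and the age, body mass index, injury, disease and antibiotic criteria all reduce that number. The back-reference that ends the sentence may mean the half-year enrolment phase and not the 320. Rates with different denominators can have different thresholds without contradiction. Moreover, 30 is a minimum and 320 an approximate maximum: enrolling 33 of 320 meets the minimum and the 10% rule, and also meets the 80% rule with up to 41 eligible students or against the target of 30.

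Most of this stands. A reader might infer that the two criteria contradict each other on every reading, that > 80% is out of reach, or that the rule gives a wrong verdict. The documents do not support that. The 80% level is out of reach only if the denominator is the whole pool, which the text does not require. The 10% sentence says what this pilot has to reach; it does not say that a shortfall makes the main trial infeasible. Its gap to 9.4% looks like rounding against an approximate figure.

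The article is also condensed, and a fuller protocol may define the denominators. That would settle the 80% rule, but the article itself states both thresholds and describes the rate by a count alone. It would not remove the mismatch between 10% and 30 of about 320.

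The defence does not supply the missing denominator. It argues for the eligible-student reading as the more natural one, and on that reading the outcome depends on an eligible count that the article does not give.

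**Conclusion.** The point holds in two parts of unequal weight.

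1. **The 10% threshold is slightly misaligned with the planned size.** Exactly 30 of 320 is 9.4%; 33 would be needed. This is small and rests on taking 320 at face value. A pool of 299 or fewer removes it.
2. **The > 80% recruitment criterion is not defined well enough to apply.** The requirement ranges from 25 recruits (target of 30) to 257 (pool of 320). With 30 recruits and eligible students as denominator, it turns on whether 37 or 38 students are eligible. This is the weightier part, because this sentence is worded as the decision on the future trial.

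The progression verdict on recruitment is therefore undetermined. It is not shown to be wrong, and the two thresholds can both be met under some readings. The conclusion rests only on the stated 30, around 320, 10% and 80%.

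**What to change.** - **Enrolment.** Replace the 10% requirement with a count that matches the sample size, for example: *at least 30 participants randomised within six months (about 9.4% of around 320).*
- **Progression.** Tie the > 80% criterion to one explicit denominator, fixed before the data are read. If the target of 30 is chosen, the criterion is met from 25 recruits, so the text must also say how that relates to the minimum of 30: for example, whether 25 to 29 recruits support a main trial although the pilot misses its own minimum.
- **Terms.** Use one name per rate and give numerator and denominator for each.
- **Reporting.** Report uptake (randomised among eligible, invited students) descriptively, with an exact confidence interval computed from the observed counts. Do not attach a confidence interval to the planned 30/320, which is a design figure and not an estimate.

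The cost is two reworded sentences in Participants and recruitment, and a screening log recording how many students were approached, eligible, invited and randomised. Sample size and study procedures for participants do not change.

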### Randomisation

Participants will be randomised in a 1:1 ratio and allocated to group one (endurance-probiotics) or group two (probiotics-endurance) via block randomisation by the study director [48]. Exclusion criteria will be injuries; diseases (e.g. inflammatory bowel diseases), an antibiotic therapy just before or during the intervention; and continuing gastrointestinal disturbances based on probiotic intake. Subjects who meet the inclusion criteria will obtain detailed information about the trial and will give written informed consent before starting the study.

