### Aims and objectives

Primary outcomes of this randomised, controlled, cross-over pilot trial are the feasibility and practicality of the intervention, the validity of the study design and the provision of a reliable estimate for sample size calculation. To assess the practicality of the intervention, the duration (60 min), frequency (three times per week) and intensity (70–80% HRpeak) of the exercise programme will be considered as well as the adherence to the daily probiotic supplementation. The validity of the study design will be assessed with regard to the collection and immediate shipping of faecal samples. A further assessment will be made considering the time commitment for participants to complete endurance training, anthropometric testing, faecal samples and food diaries. In order to evaluate the efficacy of the intervention, the influence of moderate endurance training compared to probiotic supplementation (SymbioLactComp®) on the intestinal microbiota composition and barrier function (selected mucosal and immune parameters) as well as on selected blood and saliva biomarkers (haemogram, selected cytokines) in healthy student athletes will be examined.

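### The exclusion list includes events that arise after randomisation, one of them most plainly a reaction to the study product, while the base of the retention criterion is not fixed as all randomised

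*Protocol article*

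**What the plan says.** The section Randomisation of the protocol article gives one undivided list: "Exclusion criteria will be injuries; diseases (e.g. inflammatory bowel diseases"), followed by "an antibiotic therapy just before or during the intervention; and continuing gastrointestinal disturbances based on probiotic intake". It does not say which items are checked at entry and which apply later.

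The same section sets the allocation: "Participants will be randomised in a 1:1 ratio and allocated to group one (endurance-probiotics) or group two (probiotics-endurance"). Both sequences contain the probiotic, so everyone is due to receive it in one of the two periods.

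Aims and objectives makes feasibility primary ("Primary outcomes of this randomised, controlled, cross-over pilot trial are the feasibility and practicality of the intervention") and counts towards practicality the exercise dose "as well as the adherence to the daily probiotic supplementation".

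Statistical analysis says: "Attendance and retention rates will be assessed to calculate adherence". Retention is then defined: "The retention rate will be analysed by the percentage of participants completing all sessions of the endurance training (twelve in total"), together with both shuttle runs and all four rounds of food records, blood and saliva, and stool. A closing qualifier refers to being present at each step. Retention above 80% is taken as showing that a main trial is feasible. Sample size asks for at least 30 participants.

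**The concern.** An eligibility criterion should be something that can be established before allocation. Antibiotic treatment during the intervention cannot be, on any reading. The gastrointestinal item, read plainly, is intolerance of a study treatment, and that is a result of the trial.

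In a feasibility trial, participants who cannot carry on are part of the primary result. If they are called excluded, three things can follow:

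- The retention rate can rise, because they may drop out of its denominator.
- Probiotic intolerance can be recorded as ineligibility. The retention components include no item for taking the probiotic, so it would not show there either.
- The exploratory gut-marker estimates, and the standard deviations meant for the main trial's sample size, can come from a subset selected partly by response to one of the treatments. Gastrointestinal disturbance lies close to the mucosal and microbiota outcomes.

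At stake is the decision to go on to the main trial, and the inputs for designing it.

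**Working it through.** **The plan's own figures.** The 80% is a chosen threshold. The minimum of 30 is given without a standard deviation, precision target or dropout rate. Neither can be reproduced, so the check concerns how the threshold behaves under two possible bases.

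**Inputs.** N = 30 randomised (Sample size); pass if retention exceeds 80% (Statistical analysis). Let e be the number excluded after randomisation and c the number of completers. The article gives no rates for antibiotic use, intolerance, injury or other loss, so any rate below is an assumption.

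**Formulas.**

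- All randomised: R₁ = c / N
- Excluded people removed: R₂ = c / (N − e)

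Because N − e ≤ N, R₂ ≥ R₁. Removal can raise the rate or leave it unchanged, never lower it.

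**Completers needed to pass.** This is the smallest whole c above 0.8 × (30 − e).

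| Removed (e) | Denominator | 0.8 × denominator | Completers needed | As share of 30 |
|---|---|---|---|---|
| 0 | 30 | 24.0 | 25 | 83.3% |
| 1 | 29 | 23.2 | 24 | 80.0% |
| 2 | 28 | 22.4 | 23 | 76.7% |
| 3 | 27 | 21.6 | 22 | 73.3% |

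**Worked example (assumed counts).** With 3 excluded and 4 other non-completers, c = 30 − 3 − 4 = 23. Over all randomised, 23/30 = 76.7%, which fails. With the excluded removed, 23/27 = 85.2%, which passes.

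**Chance of passing (assumed rates).** Let each participant independently be excluded with probability p, be lost for another reason with probability q, or complete with probability 1 − p − q. Summing the exact multinomial probabilities of the outcomes that pass gives:

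| Excluded, p | Other loss, q | Pass, all randomised | Pass, excluded removed |
|---|---|---|---|
| 0% | 10% | 93% | 93% |
| 0% | 15% | 71% | 71% |
| 5% | 10% | 71% | 93% |
| 5% | 15% | 43% | 71% |
| 10% | 10% | 43% | 91% |
| 10% | 15% | 20% | 68% |
| 15% | 10% | 20% | 88% |
| 15% | 15% | 8% | 62% |

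As a check, the binomial chance of at least 25 completers out of 30 at a completion probability of 0.75 is 0.203, which agrees with the two 20% entries.

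**The case against.** The strongest reply is that the article never says excluded people leave the retention denominator. Retention is a percentage of participants who complete everything. On an ordinary reading, someone stopped for antibiotics or intolerance has not completed and counts against it, and then nothing is inflated. This stands: a reader might infer that the plan does inflate retention, but the text supports only that it can. The word exclusion and the qualifier about being present at each step lean towards removal, but the latter is unclear wording and weak evidence.

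Other limits also stand:

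- **Adherence.** A reader might infer that the attendance measure is inflated in the same way. Its formula divides the mean number present by the number of sessions, not by people, so removing people does not shrink its divisor. Taken literally, fewer people present lowers it.
- **Gastrointestinal item.** The wording does not name the study product. The Introduction says many athletes use probiotics, so intolerance known from earlier use is possible, though not the plain reading. Only the antibiotic clause is certain to include events after the start.
- **Injuries.** These are undated and are an ordinary entry exclusion for a running trial. The article does not say that injuries from the programme lead to exclusion.
- **Gut-marker comparison.** Hypothesis tests and regressions are declared exploratory, and nothing says that samples already collected would be discarded.

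Finally, an article may leave analysis sets and the handling of withdrawals to a fuller document. That excuses silence about details. It does not excuse an exclusion list that, as stated, includes an event after randomisation.

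**Conclusion.** The point holds in a limited form. The list states as an exclusion criterion one event that can only follow the start and one that most plainly is a reaction to a study treatment. The primary outcome is feasibility, and the retention base is left open. Retention can therefore be raised and intolerance reclassified. The documents do not show that either will happen.

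The actual size cannot be taken from the documents. What follows from N = 30 and the strict threshold alone is that each of the first three removals lowers the bar by one completer, from 25 to 22. How often that would change the decision depends wholly on assumed event rates, and the effect is nil if nobody is removed. A reader might infer that a few exclusions are bound to reverse the decision. That is true only of particular counts and only if those people leave the denominator. The effect on gut-marker estimates and standard deviations is a possible selection effect whose direction and size cannot be determined.

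**What to change.** 1. Split the list: entry criteria are conditions present before randomisation; everything arising later is an event.
2. Calculate retention over all randomised, with those who stop counted as non-completers.
3. Report antibiotic use, injury and gastrointestinal disturbance after randomisation by sequence and period, as feasibility and tolerability results.
4. Keep these participants' available samples in the comparisons already planned, and add a sensitivity analysis omitting samples taken after antibiotics. That analysis covers the legitimate worry that antibiotics disturb the microbiota measurements.
5. Leave any clinical rule for stopping treatment as it is, but state it separately from eligibility.

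The cost is a few sentences on eligibility and the analysis base, plus one extra analysis. The retention rate may look slightly lower.
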